**Methods:**

This prospective study consists of two phases. The first phase is a cross-sectional study that will entail gathering medical records, a questionnaire survey, and laboratory testing for vitamin D status, with a planned recruitment of 414 pregnant women. The questionnaire will be utilized to assess the risk factors for vitamin D deficiency. The vitamin D status will be obtained from measurement of the vitamin D (25-hydroxyvitamin D_3_) level in the blood. The second phase is a case-control study involving a Malay ethnic cohort with vitamin D deficiency. Participants will be divided into two groups with and without HDP (n=150 per group). Genomic DNA will be extracted from the peripheral blood monocytes of participants using the Qiagen DNA blood kit, and *VDR* sequence variants will be determined using polymerase chain reaction–high-resolution melting (PCR-HRM) analysis. Sanger sequencing will then be used to sequence randomly selected samples corresponding to each identified variant to validate our PCR-HRM results. The *VDR* genotype and mutation frequencies of *BsmI*, *ApaI, TaqI,* and *FokI* will be statistically analyzed to evaluate their relationships with developing HDP.

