**Conclusions:**

The outcome of the study will identify the nonmodifiable genetic components contributing to developing vitamin D deficiency leading to HDP. This will in turn enable gaining a better understanding of the contribution of genetic variability to the development of HDP, thus providing more evidence for a need of customized vitamin D supplementation during pregnancy according to the individual variability in the response to vitamin D intake.

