## Methods

### Objectives

The objectives of this prospective study are to (1) determine the prevalence of vitamin D deficiency and associated risk factors among Malaysian pregnant women; (2) determine the frequencies of *BsmI*, *ApaI, TaqI,* and *FokI* genotypes among Malay pregnant women with vitamin D deficiency and HDP; (3) understand and associate the distributions of *VDR* genotype and allele frequencies in relation to vitamin D deficiency among Malay pregnant women; and (4) identify mutations in the *BsmI*, *ApaI, TaqI,* and *FokI* VDR gene fragments among Malay pregnant women with HDP.

This study is divided into two phases. Phase 1 is a cross-sectional study involving Malaysian pregnant women to achieve objective 1, whereas phase 2 is a case-control study among Malay pregnant women to achieve objectives 2, 3, and 4.

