### Case-Control Study (Phase 2)

#### Participants and Data

For the second phase of the study, we chose to focus on the Malay ethnic group, who make up the majority of the Malaysian population. Pregnant women of Malay ethnicity who are classified in the vitamin D deficiency group in phase 1 of the study will be recruited for phase 2. Those with a nonviable pregnancy or those who received a diagnosis of chronic hypertension prior to the current pregnancy will be excluded. The remaining participants will then be divided into two groups: those with HDP (GH, preeclampsia, eclampsia, HELLP syndrome) and those with blood pressure in the normal range.

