### Sample Size Estimation

#### Total Sample Size

A total of 414 pregnant women will be recruited for the cross-sectional study (phase 1) to determine the prevalence of vitamin D deficiency and associated risk factors (objective 1). For phase 2, a total of 150 Malaysian pregnant women with HDP will be recruited as the case group and 150 normotensive Malaysian pregnant women with vitamin D deficiency will be recruited as controls.

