### Data Analysis Plan

Data obtained from the study will be analyzed using SPSS version 27.0 (IBM Corp). Data entered will be checked for missing or suspicious values. These will subsequently be verified with the participants or omitted as missing values. Descriptive analysis will be used to summarize the sociodemographic data, anthropometric data, clinical data, vitamin D dietary intake, sun exposure, and physical activity. The prevalence of vitamin D deficiency will be expressed in frequency and percentage. The association with sociodemographic data will be analyzed using the *χ*^2^ test, independent *t* test, and ANOVA where applicable.

We will report the comparative prevalence of *BsmI*, *ApaI, TaqI,* and *FokI*
*VDR* genotypes among Malay pregnant women with vitamin D deficiency with and without HDP. Similarly, the distributions of *VDR* genotype and allele frequencies according to vitamin D deficiency among Malay pregnant women will be reported as a descriptive analysis. Any mutations found in the *BsmI*, *ApaI, TaqI,* and *FokI* VDR gene fragments among Malay pregnant women with HDP will also be described. The associations of vitamin D status, associated risk factors, and VDR genetic variants with HDP will be determined using multivariate logistic regression analysis. The level of significance will be considered at a threshold of *P*≤.05 at the 95% CI.

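### Phase 2 genotypes only vitamin D-deficient women, so it cannot estimate vitamin D status against HDP alongside VDR genotype, or compare genotypes between deficient and non-deficient women

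*Protocol article*

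**What the plan says.** **Who enters phase 2.** The abstract's Methods paragraph says: "The second phase is a case-control study involving a Malay ethnic cohort with vitamin D deficiency". Under Case-Control Study (Phase 2), Participants and Data, women of Malay ethnicity "who are classified in the vitamin D deficiency group in phase 1 of the study will be recruited for phase 2". After exclusions, "The remaining participants will then be divided into two groups", one with HDP and one with normal blood pressure.

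**Who is genotyped.** Blood Collection and DNA Extraction, and VDR Genotyping, stand under phase 2 only. The phase 1 Sampling Process describes blood for the 25(OH)D assay and nothing else.

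**What vitamin D status means.** Classification of Vitamin D Status sets three classes: deficient (below 30 nmol/L), insufficient (30-50) and normal (50 or more).

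**What is promised.** Objective 3 concerns "genotype and allele frequencies in relation to vitamin D deficiency among Malay pregnant women", and the Objectives section assigns it to phase 2. The Data Analysis Plan reports these distributions descriptively, by vitamin D deficiency. It then adds: "The associations of vitamin D status, associated risk factors, and VDR genetic variants with HDP will be determined using multivariate logistic regression analysis". Barcode-Tagged Sequencing Analysis also promises the distribution of vitamin D status for each variant.

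**What is concluded.** The abstract states: "The outcome of the study will identify the nonmodifiable genetic components contributing to developing vitamin D deficiency leading to HDP". Projected Significance repeats this in softer terms, and the closing Conclusion extends it to nonmodifiable factors for deficiency.

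**The concern.** Vitamin D deficiency is the entry condition for phase 2, yet the plan also treats it there as something that varies: as a predictor of HDP in the regression and as the axis along which genotypes are compared in objective 3. A variable used to select every participant cannot be analysed as an exposure in those participants.

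At stake are one of the three predictor groups named for the regression, the comparative part of one of the four objectives, and the abstract's main conclusion. That conclusion is offered as evidence for tailoring supplementation to the individual, so a claim without a comparison behind it matters beyond the wording.

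**Working it through.** **1. The plan's own phase 2 figure.** Sample Size Determination for the Case-Control Study uses r = 1, P* = 0.1, P1 - P2 = 0.21 - 0.11 = 0.1, and Z values of 0.84 and 1.96:

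n = (1 + 1) × 0.1 × 0.9 × (0.84 + 1.96)² / (1 × 0.1²) = 0.18 × 7.84 / 0.01 = 141.12

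The stated 141 is reproduced. What matters here is the exposure behind it. The 21% and 11% are prevalences of vitamin D deficiency in hypertensive and non-hypertensive women. Under the phase 2 entry rule those proportions are 100% and 100%, so the contrast used to size phase 2 cannot occur in it.

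**2. The status term in phase 2.** Take 150 cases and 150 controls, all deficient:

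| | Deficient | Not deficient |
|---|---|---|
| HDP | 150 | 0 |
| Normotensive | 150 | 0 |

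The odds ratio is (150 × 0) / (0 × 150) = 0/0, which is undefined. In a logistic model with an intercept and a status indicator, both columns are all ones:

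- variance of the indicator = 0;
- rank of the design matrix = 1, where 2 is needed;
- at a fitted probability of 0.5, every entry of the information matrix is 300 × 0.5 × 0.5 = 75, so its determinant is 75 × 75 - 75 × 75 = 0.

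More women of the same kind do not change this. Because genotype exists only for these women, the same holds for any model that contains both genotype and three-class status.

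**3. Objective 3.** A table of genotype by deficiency status has one filled column (deficient) and one empty column (not deficient). Frequencies in the filled column can be reported. A difference between columns cannot.

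**4. What is unaffected.** Genotype varies freely among deficient women, and HDP defines the two groups. The comparison of VDR genotype between cases and controls, which objective 2 and the Data Analysis Plan also describe, has both its margins and can be estimated.

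**The case against.** **The regression is not tied to phase 2.** A reader might infer that vitamin D status against HDP cannot be estimated anywhere in the study. The documents do not support that. The Data Analysis Plan does not name the phase or say that one joint model is meant. Phase 1 includes all three vitamin D classes and collects clinical data and medical records. An analysis there is possible in principle, without genotype. Two limits remain: HDP is not named among the phase 1 data, and women enter at any gestation, so HDP that develops after sampling would be missed. This narrows the point to phase 2 and to models with genotype.

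**Status might mean the measured level.** The assay is quantitative and the plan does not say which form enters the model. Continuous 25(OH)D does vary among deficient women. But the plan defines status by class and announces no continuous analysis, and a range cut off at 30 nmol/L answers a narrower question. This is a usable repair, but not what is written.

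**Objective 3 is descriptive.** It would be too strong to call it unanswerable, since frequencies among deficient women can be reported as planned. What cannot be delivered is the relation to deficiency that the objective asks for.

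**The Total Sample Size wording.** That section reads "150 Malaysian pregnant women with HDP will be recruited as the case group and 150 normotensive Malaysian pregnant women with vitamin D deficiency" and so states deficiency for the controls only. A reader might infer a rival design in which cases are unrestricted and deficiency looks spuriously protective. If k cases were non-deficient, the odds ratio for deficiency would be ((150 - k) × 0) / (k × 150) = 0 for any k of at least 1, and undefined for k = 0. The sentence is more likely shorthand, because the abstract, the phase 2 eligibility text and the Data Analysis Plan all describe deficient Malay women in both groups. Nor does Malaysian exclude Malay, so an ethnic imbalance between groups is not shown. The wording needs aligning but carries no weight in the conclusion. The literal reading would not rescue the analysis either.

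**Conclusion.** The point stands in this form. Within phase 2, and in any model that includes VDR genotype, the association of three-class vitamin D status with HDP is not estimable at any sample size. Objective 3 has no non-deficient comparison group and can yield only frequencies among deficient Malay women. No planned comparison supports the abstract's claim to identify genetic components that contribute to developing deficiency. The same applies to its softer version in Projected Significance and to the closing statement on nonmodifiable factors for deficiency.

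This rests on three readings of the text: status means the three stated classes, both phase 2 groups meet the phase 2 eligibility rule, and no one outside phase 2 is genotyped. It would be wrong to conclude that phase 2 as a whole fails, since VDR genotype against HDP among deficient women is untouched. Deferring detail to an analysis plan would not help, because no method restores variation that eligibility has removed.

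**What to change.** 1. **Data Analysis Plan.** Limit the phase 2 logistic model to VDR genotype and risk factors against HDP among deficient Malay women. If vitamin D is wanted as a covariate, use continuous 25(OH)D and state that its range is truncated below 30 nmol/L.
2. **Vitamin D status against HDP.** Report it, if at all, from phase 1 and without genotype, provided HDP is recorded there. Adjust for gestational age at sampling, and state that HDP arising later is missed; the adjustment does not recover those outcomes.
3. **Objective 3 and conclusions.** Restate the objective as genotype and allele frequencies, and their relation to 25(OH)D level, within deficient Malay women. Remove or narrow the claims about genetic contribution to developing deficiency in the abstract's Conclusions, Projected Significance and the closing Conclusion.
4. **Total Sample Size.** Align the wording with the phase 2 eligibility text, so that both groups are Malay and vitamin D deficient.

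The cost is mainly rewording, plus a check on whether phase 1 records HDP. The stated conclusions become narrower. If the sponsor wants to keep objective 3 as written, a genotyped group of non-deficient Malay women would be needed, which means added sampling and laboratory work.

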### Settings

This study will be carried out at Hospital Sultan Abdul Aziz Shah (HSAAS), a tertiary university hospital in Selangor, Malaysia. The hospital provides a range of health care services to the neighboring community and serves as the teaching hospital for the Faculty of Medicine and Health Sciences, Universiti Putra Malaysia. All pregnant women attending the Obstetrics and Gynaecology Department of HSAAS who fulfill the inclusion and exclusion criteria will be recruited between November 1, 2022, and March 31, 2024. A systematic random sampling method will be used to recruit the study participants for both the cross-sectional and case-control studies.

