### Cross-Sectional Study (Phase 1)

#### Participants and Data

To achieve objective 1, Malaysian pregnant women, at any stage of gestation, with a singleton viable pregnancy at the time of recruitment and who are literate in the English or Malay language will be recruited. Women with a multiple pregnancy and on vitamin D supplementation are excluded. The gestation stage will be determined from the first day of the last menstrual cycle or based on measurement of the fetal crown-rump length determined on an ultrasound scan. Pregnant women taking vitamin D supplements or those who have been diagnosed with chronic diseases that are known to affect vitamin D levels, such as autoimmune disease and cancer, are excluded from the study.

Clinical, sociodemographic, dietary intake, and anthropometric (height, weight, and BMI) data will be collected using a pro forma. The prepregnancy BMI (kg/m^2^) will be calculated by dividing the weight (kg) by the square of the height (m^2^). Weight will be determined from prepregnancy body weight recall or obtained from the woman’s antenatal booking record along with the measured height. Participants will then be interviewed by a single trained interviewer to answer a validated questionnaire to determine their risk factors associated with vitamin D deficiency.

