**(2)**

where r is the ratio of cases to controls (1 in this instance given the equal numbers in the two groups), P_1_ is the proportion of exposed individuals in the cases, P_2_ is the proportion of exposed individuals in the controls, P* is the effect size (P_1_ – P_2_), Z_β_ at 80% power is 0.84, and Z_α/2_ is 1.96 for a .05 significance level at the 95% CI.

According to Caccamo et al [6], the prevalence of vitamin D deficiency among women with GH (P_1_) and that among pregnant women without hypertension (P_2_) is 21% and 11%, respectively. Therefore, P* is determined to be 0.1 (0.21–0.11). Applying equation 2, the sample size is calculated as:

n = (1 + 1) × (0.1) × (1 – 0.1) × (0.84 + 1.96)^2^/1 × (0.1)^2^

n = 141

Considering dropout or missing samples, 10% attrition is added to the calculated sample size. Hence, our minimum number of participants in each group (cases and controls) was determined to be 150.

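### HDP cases are likely to be sampled later in pregnancy than controls, and gestation at sampling is not named in the HDP regression, so its time-varying non-genetic terms may be biased

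*Protocol article*

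**What the plan says.** **Entry (Cross-Sectional Study (Phase 1), Participants and Data).** The study takes "Malaysian pregnant women, at any stage of gestation, with a singleton viable pregnancy at the time of recruitment". Gestation is established for each woman: "The gestation stage will be determined from the first day of the last menstrual cycle", or by ultrasound crown-rump length.

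**Phase 2 (Case-Control Study (Phase 2), Participants and Data).** The source is Malay women "who are classified in the vitamin D deficiency group in phase 1 of the study will be recruited for phase 2". Because "those who received a diagnosis of chronic hypertension prior to the current pregnancy will be excluded", the cases are pregnancy-onset disease. The remaining women are split into "those with HDP (GH, preeclampsia, eclampsia, HELLP syndrome) and those with blood pressure in the normal range". No gestation window or matching on gestation is given.

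**Sampling (Settings).** "A systematic random sampling method will be used to recruit the study participants for both the cross-sectional and case-control studies". The Strengths and Limitations section calls the sampling convenience sampling instead. Neither description involves matching on gestation.

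**Model (Data Analysis Plan).** "The associations of vitamin D status, associated risk factors, and VDR genetic variants with HDP will be determined using multivariate logistic regression analysis". Three groups of terms are given, and gestation is not named in any of them. The group of associated risk factors is not itemised.

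**The concern.** A woman can be counted as a case only once HDP has appeared, whereas a normotensive woman can be counted as a control at any week. Unless something equalises the two groups, gestation at interview and blood draw will tend to be later in cases. Any factor that changes as pregnancy advances will then differ between the groups even if it is unrelated to HDP. This is ordinary confounding by time of measurement. It needs no effect of the disease on behaviour, and it would remain if every control stayed normotensive to delivery.

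At stake are the non-genetic terms of the HDP model: diet, sun exposure, physical activity, and 25(OH)D level among women who are all below the deficiency cut-off. The Strengths and Limitations section expects these factors to inform cause and effect, including the risk of developing HDP, so a spurious coefficient could be read as a modifiable risk factor.

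**Working it through.** The plan states no figure on this point, so there is none to reproduce. The check asks how large the bias could be.

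**Inputs from the article**
- 150 cases and 150 controls (Sample Size Estimation).
- Two-sided test: Z "is 1.96 for a .05 significance level at the 95% CI".
- Gestation at entry: unrestricted.

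**Inputs assumed, because the article gives none**
- The gestation range at sampling in each group, taken as uniform up to week 40.
- The drift D of a null factor, in SD units, between weeks 8 and 40.

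**Calculation A: continuous factor, two-group comparison**

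Bias = D × (mean gestation of cases − mean gestation of controls) / 32.
Standard error = √(1/150 + 1/150) = 0.1155 SD.
With z = bias/0.1155, false-positive rate = Φ(z − 1.96) + Φ(−z − 1.96).

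For cases over weeks 24-40 (mean 32) and controls over weeks 8-40 (mean 24), the gap is 8 weeks and the bias is D × 8/32 = 0.25 D. The other rows follow in the same way.

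| Cases from / controls from | Gap (weeks) | Bias for D = 0.25 / 0.5 / 1.0 | False-positive rate |
|---|---|---|---|
| 24 / 8 | 8 | 0.06 / 0.13 / 0.25 SD | 8% / 19% / 58% |
| 20 / 12 | 4 | 0.03 / 0.06 / 0.13 SD | 6% / 8% / 19% |
| 24 / 20 | 2 | 0.02 / 0.03 / 0.06 SD | 5% / 6% / 8% |

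In the first row z = 0.0625/0.1155 = 0.54, 0.125/0.1155 = 1.08 and 0.25/0.1155 = 2.17. For a factor that falls with gestation, these gaps correspond to odds ratios per SD of about exp(−0.0625) = 0.94, exp(−0.125) = 0.88 and exp(−0.25) = 0.78. Simulating that row gave 8%, 19% and 56%, in line with the formula.

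**Calculation B: binary null factor in logistic regression, with a null genotype in the same model**

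400 runs per setting. The odds of the factor are multiplied by 1.25, 1.5 or 2.0 per 10 weeks (assumed).

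| Cases from / controls from | Controls earlier than any case | Crude odds ratio | Significant at 0.05 |
|---|---|---|---|
| 20 / 12 | 8/28 = 29% | 1.10 / 1.15 / 1.33 | 6% / 10% / 20% |
| 20 / 6 | 14/34 = 41% | 1.16 / 1.30 / 1.53 | 9% / 23% / 44% |
| 28 / 12 | 16/28 = 57% | 1.21 / 1.36 / 1.72 | 12% / 28% / 63% |
| 28 / 6 | 22/34 = 65% | 1.28 / 1.55 / 1.98 | 17% / 46% / 85% |

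- With equal gestation ranges, or with no drift, the odds ratio stays near 1.0 and about 5% of runs are significant.
- After restriction to the overlapping weeks and adjustment for gestation, the odds ratio is 0.96 to 1.02 and 3% to 8% of runs are significant, which is nominal within simulation error.
- The null genotype has an odds ratio near 1.0 and 3% to 8% of runs significant even in the crude model.

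**The case against.** **The regression sentence is a summary, not a covariate list.** No covariate is named individually, the group of associated risk factors is undefined, and an article may leave the list to a fuller document. This stands against saying that gestation is omitted: it is only not named. It does not dispose of the point. Unrestricted entry without matching is fixed here, and it creates the imbalance that the model has to handle. The phase 1 section also uses risk factors to mean the questionnaire factors for vitamin D deficiency, so gestation is not the natural reading.

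**The timing is not stated.** A reader might infer that cases can only be sampled late and that each woman is sampled once. The article gives no gestational threshold for HDP, does not say when case status is fixed, and describes the phase 1 and phase 2 blood collections separately without saying whether they share a visit. A woman sampled early could become a case later. This stands, so the most that can be said is that cases are likely to be sampled later. No follow-up that would remove the difference is described.

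**The phase 2 objectives are genetic.** This stands. Objectives 2 to 4 concern VDR genotypes, alleles and mutations, which do not change with gestation. Deficiency status is constant in phase 2. 25(OH)D is truncated below 30 nmol/L, so the drifts in Calculation A do not model that term. The modifiable factors discussed in the article are mainly those for vitamin D deficiency. The bias is confined to the non-genetic terms of one model.

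**The magnitudes are unanchored.** This also stands. Moving from the first to the third row of Calculation A takes the rate at the strongest drift from 58% to 8%. The figures are scenarios, not estimates.

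**Conclusion.** The concern holds in a limited form. Entry at any gestation, pregnancy-onset cases, controls defined only by normal blood pressure, and no gestation window or matching make a difference in gestation at sampling likely. The HDP model as described does not name the variable that would correct it. Time-varying non-genetic terms may therefore show associations with HDP that reflect only when the women were sampled.

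The size cannot be fixed from the article. Under the assumptions above, the false-positive rate for a null factor runs from about 5-6%, where the drift is weak or the ranges nearly coincide, to 50% or more, where the drift is strong and the gap wide. The direction for any given factor depends on how that factor changes through pregnancy.

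Two stronger conclusions are not supported. The first is that spurious risk factors will appear, because that depends on drift and ranges that are not reported. The second is that the genotype comparison is compromised, because neither the genotype nor the constant deficiency category is distorted by this mechanism.

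**What to change.** In the Data Analysis Plan:

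1. Name gestational age at interview and blood draw as a required covariate in the HDP regression, continuous and with allowance for curvature.
2. Tabulate its distribution by case and control status.
3. Estimate the non-genetic terms within the range of gestation where cases and controls overlap. Adjustment alone would extrapolate for early controls who have no comparable cases.

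**Cost.** Gestation is already collected, so the model loses one or two degrees of freedom. Restriction also removes early controls from the non-genetic estimates. In the Calculation B scenarios this is 150 × 8/28 = 43 to 150 × 22/34 = 97 of the 150 controls. For a simple two-group contrast, the standard error would rise by a factor of √[(1/150 + 1/107)/(2/150)] = 1.10 to √[(1/150 + 1/53)/(2/150)] = 1.38. The genotype comparison needs no such restriction on account of this drift and can keep all controls.
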